2  
3 **PRINCIPAL INVESTIGATORS:** [name] MS, [name] MS

4 **PROTOCOL TITLE:** Studying the PhilAdelphia Resilience Project as a Response to Overdose  
5 (SPARROw)

6  
7 **1. INTRODUCTION AND PURPOSE:**

8  
9 **1.1. Objectives:** The objective of this proposal is to evaluate the effectiveness and  
10 implementation of two City of Philadelphia Resilience Project programs to reduce  
11 opioid overdose: (1) the Alternative Response 2 (AR2) that accompanies ambulances  
12 responding to overdoses and aims to deliver harm reduction and care linkage to people  
13 who refuse hospital transport, and (2) blight remediation of abandoned buildings and  
14 land. This application leverages a natural experiment within the Resilience Project  
15 implementation to evaluate its impact on overdose outcomes.

16  
17 We propose to address the following Specific Aims:

18  
19 **SA1: Determine the effectiveness of the Resilience Project AR2 on opioid overdose**  
20 **outcomes for EMS patients who refuse hospital transport after overdose.** Using a  
21 quasi-experimental design, we will compare the proximal overdose outcomes (rates and  
22 timing of treatment linkage) and distal overdose outcomes (non-fatal overdoses within  
23 60 days and overdose deaths within 24 months) for patients who receive AR2  
24 engagement compared to those who, due to timing or location restrictions, receive  
25 traditional EMS care alone.

26  
27 **SA2: Evaluate the impact of Resilience Project blight remediation activities on**  
28 **fatal and non-fatal opioid overdose.** Blight remediation activities vary across time and  
29 space in Kensington. We will use a difference-in-difference design to compare fatal and  
30 non-fatal overdoses in the 60 days before and after any given remediation effort  
31 compared to the same time period in two nearby locations that did not get remediated  
32 but had comparable pre-blight remediation overdose rates. We will select one control  
33 location from within Kensington and one just outside the Resilience Project geographic  
34 boundary.

35  
36 **SA3: Evaluate implementation of the Resilience Project by a) characterizing the**  
37 **fidelity of the AR2 intervention in Kensington, b) measuring factors that moderate**  
38 **AR2 fidelity, including blight, c) assessing barriers and facilitators to AR2**  
39 **implementation, and d) determining the costs for AR2 and blight remediation**  

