**Inclusion criteria for the comparator group include all EMS encounters where:**

- The encounter is for a presumed overdose
- Patients are at least 18 years of age
- Located within the Kensington area (AR2 dispatch zone) and areas that are immediately adjacent
- From May 1, 2019 to April 30, 2021 (24 months)

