## **2.4. Subject Recruitment and Screening:** For people who interact with the AR2 or traditional EMS, we will not be doing any specific recruitment to the study. The

population will be added to our study retrospectively and followed using city administrative data. Sources of research material consist primarily of administrative data already collected by the City of Philadelphia including information about all AR2 encounters, EMS data regarding non-fatal opioid overdose dispatches, Medical Examiner data regarding fatal opioid overdoses, and Department of Behavioral Health data regarding substance abuse treatment. We will collect data over a 2-year time period.

We will recruit AR2 team members to participate in semi-structured qualitative interviews through talking with them directly about the study. We will not be recruiting AR2 team members via flyers or posters. We will rely on a snowball sampling technique, where AR2 team members that we speak with directly are able to refer to us other individuals they believe would be eligible to be interviewed.

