## **2.5. Early Withdrawal of Subjects: N/A**

## **2.6. Vulnerable Populations: N/A**

## **2.7. Populations vulnerable to undue influence or coercion: N/A**

# **3. STUDY DESIGN:**

## **3.1. Design:**

**AIM 1: Determine the effectiveness of the Resilience Project AR2 on opioid overdose outcomes for EMS patients who refuse hospital transport after overdose.**

a. **Rationale and theoretical framework:** Commonly, in Philadelphia and elsewhere, people who refuse transport to an ED after their overdose are at particular risk for repeat overdose and death as they typically do not receive, at the time of the event, referral to treatment, counseling, or take-home naloxone that could be obtained through “warm handoff” programs at the hospital. This gap in prevention and treatment may contribute to significant levels of morbidity and mortality. The AR2 targets this unique and high-risk group of opioid users at the time and place of their overdose. Our evaluation of the AR2 will be guided by the Quality Framework for Emergency Treatment of Opioid Use Disorder as outlined by Samuels and colleagues. In this framework, emergency care harm reduction interventions and treatment can be implemented and evaluated through a Donabedian structure-process-outcome perspective to assess a prehospital emergency approach to opioid use. In Figure 7 we adapt this framework to the AR2 in which high quality prehospital care has the structural capacity to provide take-home naloxone and referral to evidence based treatment programs with immediate availability, harm reduction and treatment referral processes are delivered with high fidelity, and people who overdose are linked to care and subsequently are less likely to experience non-fatal and fatal overdose outcomes.

- b. **Study design:** This quasi-experimental evaluation of the effectiveness of the AR2 will compare rates and time to treatment linkage, non-fatal overdoses within 60 days, and deaths within 24 months for people in the Kensington neighborhood who overdose, refuse EMS transport, and receive AR2 services with those who refuse EMS transport but for whom the AR2 is not dispatched.

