- The ARU delivers six core services on scene to patients who refuse transport to the hospital: 1) dispensing of take-home naloxone, 2) referral to a treatment facility that has immediate availability and can provide MAT, 3) transportation to the facility, 4) family engagement, 5) acquisition of patient telephone information for follow-up, and 6) connect over the phone with the patient in follow-up. If the ARU vehicle arrives after the ambulance, ARU staff provide backup support focused on harm reduction and linkage to care as needed. ARU interventions can occur whether or not naloxone has been administered. These services are, in other settings, limited to hospital-based and fixed community-based sites and are largely outside of the scope of traditional EMS care. While EMS has the capacity to provide take-home doses of naloxone (depending on availability), anecdotally uptake has been low in Philadelphia. Moreover, traditional EMS does not have the capacity to refer patients to treatment programs, provide transportation directly to treatment programs, or follow up with people who have experienced overdose. These patients, many of who are revived by naloxone, are at particularly high risk of repeat overdose and death and do not typically have access to harm reduction or OUD treatment in locations where they live and/or use drugs. Based on total EMS encounters for overdose in Philadelphia -- including those that receive naloxone and those that don't -- and our knowledge of EMS transport refusal rates in Kensington (approximately 25%-30%), we estimate between 300 and 500 ARU engagements per year, or 600-1000 engagements over our two-year study period.

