556 study period, we will consider analyses of patients with multiple encounters over the  
557 study period, possibly switching from comparison to intervention group, while taking  
558 care to avoid survivor bias. We will follow each patient from first encounter until  
559 either a subsequent overdose or death, whichever comes first. The following plan  
560 includes three designs - a paired encounter analysis, a comparison across time  
561 periods, and a difference-in-difference analysis. Our preferred approach to minimize  
562 the risk of confounding is the paired encounter analysis, but for some outcomes the  
563 anticipated number of paired encounters would provide insufficient power. We can  
564 address this limitation in statistical power by comparing outcomes across different

time periods when the AR2 is operating and when it is not, with a slightly greater risk of confounding, but likely to have greater power. A difference-in-difference analysis is our final fallback position.

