- b. **Paired encounter analysis.** For the analysis of paired encounters (one AR2 and a non-AR2 occurring while the AR2 was on another call), we will use an exact McNemar's test for paired data for 0/1 outcomes (death, relapse) and a Cox proportional hazards model for paired data for censored time to event outcomes (time to treatment linkage, time to subsequent overdose). For each AR2 encounter we try to identify a non-AR2 encounter at the same time period within the AR2 response zone. If we find one, these pair of encounters are labeled as a pair and we will follow the patients for 60 days for linkage and non-fatal overdose, and 24 months for fatal overdose, and record outcomes. If multiple non-AR2 encounters happen simultaneously, then conditional logistic regression and stratified Cox models will extend the analysis from a 1-to-1 pairing to a 1-to-many matching. For our power calculations we assume a 1-to-1 pairing, a one-sided test for a reduction in adverse outcomes with  $\alpha = 0.05$  and a power level of at least 0.80. To detect a 50% reduction in the death rate attributable to the AR2 (assumed reduction from 10% to 5%), we need 370 pairs of encounters. To detect a 50% reduction in the rate of repeat non-fatal overdoses (from 30% to 15%), we need 105 pairs of encounters. To detect a 50% reduction in the hazard rate of time to subsequent overdose (equivalent to roughly 19% having a subsequent overdose within one year to 9.5%), we need 200 pairs of encounters. To detect an increase of 50% in the odds of seeking treatment within 60 days of an overdose (from 26% seeking drug treatment after an overdose within 60 days to 35% with AR2), we need 360 pairs of encounters.

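### The Aim 1 rule that ends follow-up at the first repeat overdose contradicts the 24-month death outcome, and the end date of the death data is unclear

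*Protocol*

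**What the plan says.** Four parts of the protocol bear on how long a patient is followed for death.

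- **Section 5.5, Aim 1 a** sets a general rule before the three designs are introduced: follow-up runs from first encounter until "either a subsequent overdose or death, whichever comes first". Death is not excepted.
- **Section 5.5, Aim 1 b** (paired encounters) says the team will "follow the patients for 60 days for linkage and non-fatal overdose, and 24 months for fatal overdose". Nothing there stops at a repeat overdose. Death is a 0/1 outcome tested with an exact McNemar test, with 370 pairs to detect 10% against 5%.
- **Sections 1.1 (SA1) and 3.1 (Aim 1 b)** define the distal outcomes as "non-fatal overdoses within 60 days, and deaths within 24 months".
- **Section 5.5, Aim 1 c and d** (time discontinuity, difference-in-difference) power the same 10% to 5% reduction, with 380 encounters per arm and 600 per area and time period. They give no follow-up window for death.

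On calendar time, section 2.2 accrues encounters from May 1, 2019 to April 30, 2021. Section 2.4 lists the data sources, including the Medical Examiner, and then says "We will collect data over a 2-year time period". Section 4.6, Subject Follow-Up, is marked N/A.

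**The concern.** Under the general rule, a patient who survives a repeat overdose in month 3 and dies in month 10 is not counted as a death. Under the paired-design rule the same patient is. Two analysts could therefore obtain different mortality results from one protocol.

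The general rule also does not act equally on the two groups if AR2 works. The protocol assumes that AR2 halves repeat overdose, so comparators would leave follow-up more often and lose more deaths, which pulls the mortality contrast toward no effect. Neither the McNemar test nor the binomial test of proportions allows for shortened follow-up. The same rule would drop treatment linkage that follows a repeat overdose within the 60 days.

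The calendar question is separate. If death data end when accrual ends, only the earliest entrants have 24 months of follow-up.

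**Working it through.** **Inputs from the protocol (section 5.5, Aim 1 b).** One-sided alpha 0.05 and power 0.80. Death 10% against 5%. Subsequent overdose about 19% against 9.5% within one year. Repeat non-fatal overdose 30% against 15%, with a 60-day outcome window.

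**Assumptions added here.** The 10% and 5% refer to 24 months. Hazards are constant, pair members are independent, and death is independent of non-fatal repeat overdose. Entry is uniform over 24 months where a calendar cut-off is applied. A first subsequent overdose that is fatal still counts as a death.

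**1. The plan's own figures.** The discordant probabilities are 0.10 × 0.95 = 0.095 and 0.05 × 0.90 = 0.045. The exact one-sided McNemar test at 370 pairs has power 79.8%, and 373 pairs reach 80%. For the unpaired design, two proportions with continuity correction need 382 per arm, against 380 stated. Both figures reproduce, but only with complete 24-month death data.

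**2. Hazards per year.** Death: −ln(0.90)/2 = 0.0527 and −ln(0.95)/2 = 0.0256. Repeat overdose in comparators: −ln(0.81) = 0.2107; halved with AR2, 0.1054.

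**3. General rule applied, yearly overdose rates.** Counted deaths = d/(d+o) × (1 − exp(−2(d+o))), where d is the death hazard and o the overdose hazard.
- Comparator: 0.0527/0.2634 × (1 − 0.90 × 0.81²) = 0.200 × 0.4095 = 8.2%.
- AR2: 0.0256/0.1310 × (1 − 0.95 × 0.81) = 0.196 × 0.2305 = 4.5%.
- The ratio is 0.55 and exact power at 370 pairs is 61%. Using 9.5% per year for AR2 instead of a halved hazard gives 60%.
- Comparators lose 1.8 percentage points of deaths and AR2 patients 0.5. With 19% and 9.5% per year, mean follow-up is 18.7 against 21.2 months.

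**4. General rule applied, 60-day rates and no repeat overdose afterwards.** Counted deaths are those in the first two months, plus those in the remaining 22 months among patients still followed.
- Comparator: 0.0074 + 0.6939 × 0.0921 = 7.1%.
- AR2: 0.0039 + 0.8464 × 0.0459 = 4.3%.
- The ratio is 0.60 and exact power is 45%.

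**5. Calendar cut-off alone.** With uniform entry, the average counted proportion is 1 − (1 − exp(−2d))/(2d).
- Comparator: 1 − 0.10/0.1054 = 5.1%. AR2: 1 − 0.05/0.0513 = 2.5%.
- The ratio stays at about 0.50 and exact power is 51%.

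| Reading | Deaths, comparator vs AR2 | Ratio | Power, 370 pairs | Needed per arm, unpaired |
|---|---|---|---|---|
| Full 24 months | 10.0% vs 5.0% | 0.50 | 80% | 382 |
| Stop at overdose, yearly rates | 8.2% vs 4.5% | 0.55 | 60-61% | about 605 |
| Stop at overdose, 60-day rates | 7.1% vs 4.3% | 0.60 | 45% | about 891 |
| Calendar cut-off only | 5.1% vs 2.5% | 0.50 | 51% | about 762 |

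With both limits together, power is about 40% at the yearly rates and 26% at the 60-day rates.

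**The case against.** The strongest reply is that the protocol already contains the right rule. Aim 1 b is specific to each outcome, gives death its 24 months and linkage its 60 days, and belongs to the preferred design. The general sentence comes just after the discussion of repeat encounters and fits the time-to-subsequent-overdose outcome. There are no study visits: deaths come from Medical Examiner records and linkage from behavioral health claims, so a repeat overdose removes nobody from the files. The 2-year sentence matches the encounter window and the engagement estimate in section 3.1 ("600-1000 engagements over our two-year study period"), and a data cut-off date is commonly left to an analysis plan.

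Much of this stands. A reader might infer that deaths will certainly be lost and the power for death is gone. The documents do not support that: they hold two rules, and the loss arises only where the general one is applied. A reader might also infer that the 2-year limit cuts comparators harder. It does not, given similar entry times. Nor should the 30% in 60 days be carried forward as a constant hazard for two years. That would bring power to about 4%, but it implies 1 − 0.7⁶ = 88% with a repeat overdose within a year, against the protocol's own 19%.

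The reply does not remove the conflict. The specific rule is written for paired encounters only. The protocol expects some outcomes to move to the other designs for lack of pairs, and there the general sentence is the only follow-up rule. That the files would permit full ascertainment makes the correction cheap, but does not say which rule the analyst should use.

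**Conclusion.** The point holds as a contradiction to be reconciled, sharpest for the time-discontinuity and difference-in-difference designs. If the general stop governs death, the risk ratio is diluted from 0.50 to about 0.55-0.60 and power at 370 pairs falls from 80% to between 45% and 61%. The dilution is differential only under the hypothesised AR2 benefit on repeat overdose. The sizes rest on the assumptions listed above; if patients who overdose again also die more often, the loss is larger.

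The calendar question is conditional too. It matters only if the 2-year data collection also closes the death data. In that case power is about 51% with the ratio essentially unchanged, so it is a loss of information and not a bias between arms.

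**What to change.** 1. In section 5.5, Aim 1 a, limit the stop at first overdose to the time-to-subsequent-overdose outcome.
2. State once, for all three designs, that fatal overdose is ascertained for 24 months and treatment linkage for 60 days from the index encounter, regardless of any intervening non-fatal overdose.
3. In section 2.4, separate the encounter window from the outcome window, and have the Medical Examiner extract run to 24 months after the last encounter: April 30, 2021 plus 24 months is April 30, 2023.
4. If the extract must stop earlier, analyse death with the paired or stratified Cox model already in the plan, with administrative censoring, and restate the power for death.

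The cost is reworded text and a later administrative extract, which delays the mortality result. No new patients or procedures are needed.

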- c. **Comparisons across time discontinuities.** For outcomes underpowered with a paired analysis, we will compare AR2 encounters during AR2 operational hours (10AM-6PM) to non-AR2 encounters outside of AR2's operational hours (6PM-10AM) within the Kensington zip code. Since comparison encounters will not be occurring at the same times as the AR2 encounters, there is a risk of confounding. We will first assess whether AR2 and non-AR2 patients encountered differ on likely confounders (e.g. age, race, sex, substance use profile such as type of drug, injected or not). Ideally focusing exclusively on patient encounters closest to AR2 time boundaries (near 10AM and 6PM) will provide sufficient observations and minimize the risk of confounding. If we find no differences (e.g. patients overdosing earlier in the day resemble those who overdose later in the day) then we will analyze the data as a simple binomial test of proportions (for 0/1 outcomes) or estimate the hazard ratio (for time to event outcomes). If we do find differences, then we will propensity score reweight comparison cases on age, sex, race, and substance use profile so that they do match. The following power calculation assumes no propensity score reweighting, but if propensity score reweighting is needed, the effective sample size, computed as  $(\sum w_i)^2 / \sum w_i^2$  where  $w_i$  is the propensity score weight, will need to equal the needed sample size in the power analysis. This depends on how many comparison encounters closely resemble the AR2 patients. To detect a 50% reduction in the death rate

attributable to the AR2 (assumed reduction from 10% to 5%), we need 380 encounters in each arm. To detect a 50% reduction in the rate of repeat overdoses (from 30% to 15%), we need 105 encounters in each arm. To detect a 50% reduction in the hazard rate of time to subsequent overdose (equivalent to roughly 19% having a subsequent overdose within one year to 9.5%), we need 200 encounters in each arm. To detect an increase of 50% in the odds of seeking treatment within 60 days of an overdose we need 380 encounters in each arm.

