- d. **Difference-in-difference.** To further protect against confounding, we will compare encounters across times and places simultaneously. If within zip code 19134 those who overdose earlier in the day differ from those who overdose later in the day, but those differences are also reflected in the population outside zip code 19134, then a difference-in-difference analysis can use encounters outside 19134 to learn the expected difference between patients with early overdoses and later overdoses and appropriately adjust the within 19134 estimated treatment effect. For example, let  $\hat{p}_{01} - \hat{p}_{00}$  represent the estimated difference in the rate of seeking treatment for those outside 19134 during AR2 operating hours ( $\hat{p}_{01}$ ) and the rate of seeking treatment for those outside 19134 and outside of AR2 operating hours ( $\hat{p}_{00}$ ). Since the AR2 never operates outside of 19134 this difference captures the expected difference treatment seeking for those who overdose at different time periods. Then the difference-in-difference estimate  $((\hat{p}_{11} - \hat{p}_{10}) - (\hat{p}_{01} - \hat{p}_{00}))$  adjusts the treatment contrast within 19134 ( $\hat{p}_{11} - \hat{p}_{10}$ ) by subtracting off the observed difference by time of day for an untreated sample ( $\hat{p}_{01} - \hat{p}_{00}$ ). In practice, we compute ratios of odds ratios for 0/1 outcomes and ratios of hazard ratios for time-to-event outcomes.
- Because difference-in-difference estimates require estimation of three comparison quantities, the estimates are less precise and have greater sample size demands. We compute the number of encounters needed in each area (within 19134 and outside but near 19134) and time period (AR2 operational hours and AR2 non-operational hours). To detect a 50% reduction in the death rate attributable to the AR2 (assumed reduction from 10% to 5%), we need 600 encounters in each area in each time period. To detect a 50% reduction in the rate of repeat overdoses (from 30% to 15%), we need 170 encounters in each area and time period. To detect a 50% reduction in the hazard rate of time to subsequent overdose, we need 320 encounters in each area and time period. To detect an increase of 50% in the odds of seeking treatment within 60 days of an overdose we need 700 encounters in each area and time period.

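### The two control rates used to size repeat overdose conflict on the only window the protocol gives, and the follow-up for time to overdose is stated two ways, so the sizes cannot be relied on until reconciled

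*Protocol*

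**What the plan says.** Protocol section 3.1, AIM 1 b, names the outcomes as "non-fatal overdoses within 60 days, and deaths within 24 months"; section 1.1 (SA1) gives the same windows. Section 5.5, AIM 1 b (paired encounter analysis), will "follow the patients for 60 days for linkage and non-fatal overdose, and 24 months for fatal overdose".

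The sizing in that paragraph assumes 1-to-1 pairs, "a one-sided test for a reduction in adverse outcomes" at the 0.05 level, and power of at least 0.80. It contains two statements on repeat overdose:

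- Binary outcome: "To detect a 50% reduction in the rate of repeat non-fatal overdoses (from 30% to 15%), we need 105 pairs of encounters". This sentence names no window.
- Time to subsequent overdose, hazard halved: "equivalent to roughly 19% having a subsequent overdose within one year to 9.5" per cent, for which 200 pairs are required.

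Item c (time discontinuities) repeats both sets of rates: "To detect a 50% reduction in the rate of repeat overdoses (from 30% to 15%), we need 105 encounters in each arm", and 200 per arm for the 19% figure. Item d (difference-in-difference) repeats the first: "To detect a 50% reduction in the rate of repeat overdoses (from 30% to 15%), we need 170 encounters in each area and time period". It gives 320 per cell for the halved hazard without restating a rate.

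Item a, which introduces all three designs, follows each patient from the first encounter to a further overdose or death and sets no 60-day limit.

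**The concern.** Non-fatal overdose is a subset of any overdose, and 60 days lies within one year. If the 30% is a 60-day risk, it cannot stand beside a one-year risk of 19% in the same comparator patients. This needs no assumption about the hazard.

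Separately, the 200 pairs draw on a year of events, but the paragraph that contains them follows non-fatal overdose for 60 days.

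The figures have a use beyond description. Section 5.5 a and c send outcomes that are underpowered in the preferred paired design to the time-of-day comparison, and then to difference-in-difference. The protocol itself says the time-of-day comparison carries more risk of confounding. A requirement of 105 pairs rather than about 1,000 could reverse that choice for a main Aim 1 outcome.

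**Working it through.** **Inputs (section 5.5 b).** One-sided 0.05, power 0.80, 1-to-1 pairs, exact McNemar for 0/1 outcomes, paired Cox for time to event. Rates: 30% vs 15%; 19% vs 9.5% at one year; hazard ratio 0.5. My assumptions: independent pair members throughout, and constant hazard where stated.

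**1. Reproducing 105 pairs.** Discordant probabilities are 0.30 × 0.85 = 0.255 and 0.70 × 0.15 = 0.105, in total 0.36. Exact one-sided McNemar power is the sum over m of Bin(m; n, 0.36) × P(reject | m), with the m discordant pairs split at 0.255/0.36 = 0.708. At n = 105 the power is 0.798; 0.80 is reached at n = 106. The stated figure reproduces.

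**2. Reproducing 200 pairs.** With hazard ratio 0.5, the first event in a pair falls on the comparator with probability 1/1.5 = 2/3, against 1/2 under the null. Informative pairs needed: [(1.645 × 0.5 + 0.842 × √(2/9)) / (1/6)]² = 53.5. The chance that a pair has an event in one year is 1 − 0.81 × √0.81 = 1 − 0.81 × 0.90 = 0.271. So 53.5 / 0.271 = 197 pairs. Freedman's formula gives 55.6 events / (0.19 + 0.095) = 195 per arm. The stated figure reproduces, but only with about a year of events.

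**3. Branch A: 19% per year is right.** The 60-day risk depends on how early events fall.

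- Constant hazard: −ln 0.81 = 0.2107 per year. Comparator 60-day risk is 1 − exp(−0.2107 × 60/365) = 3.4%; with the hazard halved it is 1.7%.
- Extreme: every event falls by day 60, so 19% vs 9.5%.

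| 60-day risks | Exact power, 105 pairs | Pairs for 0.80 |
|---|---|---|
| 3.4% vs 1.7% | 0.07 | about 1,180 |
| 19% vs 9.5% | 0.56 | about 185 |

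Uncorrected normal-approximation formulas give fewer pairs (169 and 1,085), but the planned test is exact. At 170 pairs its power for 19% vs 9.5% is 0.77.

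For time to overdose with follow-up stopped at 60 days and constant hazard, the chance of an informative pair is 1 − exp(−0.2107 × 1.5 × 60/365) = 0.0506. Then 200 × 0.0506 = 10.1 informative pairs against 53.5 needed, with power about 0.27 (0.30 by Schoenfeld's formula). The requirement would be 53.5 / 0.0506 = 1,057 pairs. If all events fell by day 60, 200 pairs would still give 0.80 or slightly more. With a full year of follow-up, 200 pairs are adequate (step 2).

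**4. Branch B: 30% at 60 days is right.** 105 pairs give about 0.80. With the hazard halved, the intervention risk is 1 − √0.70 = 16.3%. The chance of an informative pair is 1 − 0.70 × 0.837 = 0.414, so 200 pairs yield about 83 against 53.5 needed, with power about 0.93 (0.95 by Schoenfeld). The one-year risk is then at least 30%, and under constant hazard 1 − 0.70^(365/60) = 89%. It cannot be 19%.

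**5. Branch C: the 30% has a longer, unstated horizon.** At the hazard giving 19% per year, 30% is reached at ln 0.70 / ln 0.81 = 1.69 years. The rates then agree, but 105 pairs size an outcome over about 1.7 years, while the protocol analyses 60 days.

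**The case against.** The strongest reply is that nothing here is an arithmetic error. Both sizes follow from their own inputs, and the protocol does not show which rate is wrong. That stands. A reader might infer that the stated sizes fail to give 0.80 power; the documents support this only if 19% per year is the true rate. Under Branch B both sizes suffice, even with 60-day follow-up.

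Second, the 60 days on the 30% is inferred from the outcome definition and is not written beside the figure. That also stands, so calling the two rates impossible under any reading goes too far. Branch C reconciles them, but at the price of sizing an outcome that is not analysed, so a correction is needed either way.

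Third, section 5.5 a follows patients to overdose or death without a cap, and time to subsequent overdose is listed as an outcome of its own. A reader might take 60-day follow-up as settled for it; it is not. The uncapped statement and the 60-day statement have to be reconciled.

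Fourth, it is tempting to say that 105 pairs could never be enough under 19% per year. That rests on independent pair members. At 19% vs 9.5% with a within-pair correlation of 0.5, an extreme case, exact power is 0.83.

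Finally, this is a retrospective study with a fixed encounter window, so the sizes do not set enrolment. True, but they do govern the choice of design. The protocol gives no expected number of pairs, so it cannot be said that repeat overdose will in fact be misclassified as adequately powered.

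**Conclusion.** The point holds as a conflict between planning inputs and between follow-up statements. On the only window stated for repeat non-fatal overdose, 30% and 19% cannot both describe the comparator group, and the 200 pairs presuppose about a year of events that one of the two follow-up statements does not allow. Power of 0.80 therefore cannot be relied on until these are settled.

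The possible size is large. Under 19% per year, 105 pairs could need to become anything from about 185 to about 1,180. Section 3.1 expects 600 to 1,000 engagements over two years. Even if every one were paired, exact power at 3.4% vs 1.7% would be 0.52 to 0.74. Under 30% at 60 days there is no shortfall, only a wrong one-year figure. The conflict itself rests on the protocol's 60-day outcome definition; the numerical range rests on independent pair members and, at its low-risk end, on constant hazard.

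**What to change.** In section 5.5, AIM 1:

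- Write a horizon beside the 30%, and derive the 60-day and one-year rates from one consistent source.
- State one follow-up period for time to subsequent overdose, reconciling items a and b. Go beyond 60 days only as far as the EMS data cover, with late entrants censored. The protocol speaks of two years of data collection and includes encounters to April 30, 2021, so a full year of look-ahead for every patient should not be presumed.
- Recompute and restate the repeat-overdose sizes: 105 and 200 pairs in item b (using the planned exact test for the binary outcome), 105 and 200 per arm in item c, and 170 and 320 per cell in item d.
- Decide again from the new figures which outcomes leave the paired design.

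The cost is recalculation and wording. The restated figures may be less favourable, and the paired design may prove unable to power the 60-day outcome.
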